## Abstract

**Background:**

Poor perinatal mental health and maternal sensitivity towards a child in the early years can carry a long-term cost to individuals and to society, and result in negative child outcomes such as poor mental health and social emotional issues. Despite the recognition of early intervention and prevention, there is mixed evidence regarding antenatal parenting interventions that aim to enhance perinatal mental health and maternal sensitivity to prevent negative child outcomes. ‘Baby Steps’ is a relationship-based antenatal and postnatal parenting programme. The service evaluated in this study is delivered in a low-income and ethnically diverse community via Better Start Bradford.

This study aims to assess whether the universally, and remotely delivered Baby Steps programme is effective in improving postnatal maternal sensitivity (primary outcome) and postnatal maternal mental health (secondary outcome) when compared to services as usual 6–10 weeks post-birth. It will also assess differences in birth outcomes, and differences in the prevalence of poor perinatal mental ill health through routine data. The feasibility of collecting cost and health related resource use data for a future economic evaluation will be explored.

**Methods:**

The study is a quasi-experimental evaluation in a single centre. All participants are drawn from Born in Bradford’s Better Start (BiBBS) interventional family cohort study. Intervention participants will be matched to a demographically comparable control group using propensity score matching. The required minimum sample is *n* = 130 (ratio 1:1) to detect a medium effect (± 2.35, *d* = .50) on the primary outcome—maternal-child sensitivity, using the Mothers Object Relations Scale Short Form (MORS-SF). Secondary outcomes include the Patient Health Questionnaire (PHQ-8), Generalised Anxiety Disorder assessment 7 (GAD-7), identification of poor perinatal mental health through routine data, and birth outcomes (delivery method, gestation period, low birth weight). Service delivery costs and health resource use will be gathered from routine data.

**Discussion:**

This study will evaluate the effectiveness of Baby Steps for enhancing maternal-child sensitivity and maternal mental health when delivered universally and remotely. The findings regarding programme effectiveness, process, and costs will be relevant for researchers, service commissioners, and service staff.

**Trial registration:**

This study was prospectively registered with ISRCTN (22/04/2022, ISRCTN12196131).

**Supplementary Information:**

The online version contains supplementary material available at 10.1186/s12889-023-15111-1.

## Background

The perinatal period refers to both pregnancy (the antenatal period) and the first 12 months after childbirth (the postnatal period) [37]. We use the terms ‘women’ and ‘maternal’ to refer to birthing parents, we recognise however that not all birthing parents are women. Perinatal mental health problems carry an estimated long-term cost to society of £6.6 billion for each 1-year cohort of births, with most of this cost relating to negative impacts on the child rather than the mother [4]. Perinatal mental health problems can have an adverse effect on maternal perceptions of infant temperament and mother–child bonding [18, 35], and on the cognitive, behavioural, and psychomotor development of their child [31, 36]. Improving perinatal mental health is therefore crucial for improving mother–child bonding, to foster the development of children’s attachment, social and emotional competence, cognitive functioning, physical health, and mental health [19, 36, 42].

Specifically within the postnatal period, postnatal depression affects an estimated 10–19% of women globally [29]. In the UK, 11% of women have a diagnoses or symptoms of postnatal depression, with increased risk for those living in the most deprived areas [55]. A systematic review revealed that women belonging to ethnic minority groups are at an increased risk of reduced identification and management of poor mental health in the perinatal period [41].

Parenting programmes are those which help parents and their children to develop positive behaviours and relationships [24]. Early parenting programmes that reduce parental psychological distress and improve parent–child relationships during the perinatal period have the potential to reduce the economic burden on society and improve outcomes for children [1, 2]. However, systematic reviews which have synthesised evidence about these interventions have shown mixed results depending on the outcome examined.

A systematic review and meta-analysis of maternal antenatal parenting education programmes found that programmes had a significant positive effect on maternal mental health outcomes of stress and self-efficacy, but not on maternal anxiety or depression. There was also no evidence that programmes improved maternal physical outcomes or foetal birth outcomes, but caesarean birth rates and epidural anaesthesia rates were lower [30]. Similarly, a systematic narrative review of psychological interventions delivered during the antenatal period found that the effectiveness of these interventions was mixed, highlighting the need for more research into effective interventions in the antenatal period to prepare parents for parenting [6].

A meta-analytic review of online parenting programmes found interventions demonstrated medium sized effects on both parent and child outcomes [38]. However, this review combined heterogeneous studies such as targeted and universal programmes, and cognitive, behavioural, and attitude outcomes. Further, this review was published prior to COVID-19. Since the COVID-19 pandemic, many services have had to adapt dynamically to both the changing guidelines and to service user’s willingness to engage with services.

Related to co-parenting, a meta-analysis of interventions that focus on promoting effective co-parenting during the transition to parenthood found that they had small positive effects on couple adjustment, parent stress, child and parent mental health, and reduced child abuse [40]. The most effective interventions started in pregnancy and continued through the perinatal period, with a minimum of 5 sessions. However, it remains unknown which groups of parents benefit most from what kind of intervention with regards to the level of their social risk (e.g. levels of deprivation, ethnic group).

### The Baby Steps programme

Baby Steps is a parenting programme that was developed by the UK’s National Society for Prevention of Cruelty to Children (NSPCC). Baby Steps was developed as a 9-session, relationship-based, antenatal and postnatal parent education programme designed for vulnerable and socially excluded parents who often face challenges and ‘overload’ in pregnancy and early parenting. In a pre-post study of Baby Steps, Coster et al., [17] found positive changes in measures of both maternal and paternal attachment and warmth, lower rates of adverse birth outcomes, and reductions in maternal and paternal anxiety. However, this study was not undertaken by independent researchers, and was not designed to ascertain causal effectiveness. A qualitative study found that both mothers and fathers felt more confident in their parenting and had developed stronger support networks and communication with their partners and babies [12]. While this preliminary evidence is encouraging, a robust and independent evaluation of Baby Steps is required to ascertain causal intervention effectiveness.

The current study evaluates the Baby Steps programme as delivered in the Better Start Bradford area by Action for Children. In response to the COVID-19 pandemic in March 2020, Baby Steps in Better Start Bradford moved to a remote delivery model with condensed programme content. For the condensed programme content, Baby Steps in Better Start Bradford have developed a logic model [15]. Baby Steps also moved from a targeted to a universal offer in February 2022, which removed all eligibility criteria from the programme to enable all parents in Better Start Bradford to attend (see method section for more details). Due to the local adaptation of Baby Steps, and the potential uptake of the remote, universal, model more widely, it is timely and crucial to establish the effectiveness of the model and explore its associated costs.

### Objectives

The current study will examine the causal effectiveness of the Baby Steps intervention in a real-world setting, within a socioeconomically deprived and ethnically diverse area in Bradford. Baby Steps is commissioned by Better Start Bradford and delivered by Action for Children. The authors of this study are independent of the delivery or design of the service.

This study will use a matched-control comparison group. The specific aims of this study are to (1) assess whether the universally and remotely delivered Baby Steps programme is effective in improving the primary outcome of postnatal maternal sensitivity and (2) the secondary outcome of postnatal maternal mental health when compared to services as usual at 6–10 weeks postnatal. This study also aims to (3) assess whether the effects of Baby Steps on postnatal maternal sensitivity are mediated by postnatal maternal mental health.

This study has additional objectives with outcomes nested in routinely linked data, however, it will be underpowered to ascertain causal effectiveness in these outcomes. We aim to (4) assess differences in birth outcomes (delivery type, weight, gestation, feeding) and (5) assess differences in the identification and prevalence of poor perinatal mental ill health inferred through routine data linkage across the two groups. Finally, the economic analysis of this study will (6) estimate the cost of the intervention (including delivery and training to deliver Baby Steps) and (7) assess the feasibility of collecting health related resource use data for a future full economic evaluation.

## Methods/Design

### Study design

The study is a quasi-experimental evaluation with an intervention and matched control group in a single centre. In the absence of guidelines for quasi-experimental protocols, we have used the Strengthening the Reporting of Observational Studies in Epidemiology (STROBE) [25] guidelines for reporting methods in this protocol (see Additional file 1: Appendix A).

### Study setting

This study is set in Bradford, a city in Northern England with high levels of socioeconomic deprivation and a large ethnic minority population [10]. Baby Steps is currently being delivered by Action for Children through the Better Start Bradford programme. Better Start Bradford is part of network of five ‘Better Start’ programmes around the UK funded by The National Lottery Community Fund with the aim to improve the life chances of over 60,000 children living in some of the poorest parts of England. Within Bradford, the initiative is delivered in three areas: Bowling and Barkerend, Bradford Moor and Little Horton (see https://www.betterstartbradford.org.uk/).

Born in Bradford’s Better Start (BiBBS) is an interventional family cohort study, which runs in parallel to Better Start Bradford and is designed to support effectiveness evaluations of Better Start Bradford’s early life interventions [21]. BiBBS is a part of the Born in Bradford (BiB) family of studies [53]. All mothers and children in the BiBBS cohort have in-depth baseline data captured during pregnancy, and consent to routine linkage to their health and education records as well as information about intervention participation. BiBBS includes an additional questionnaire to all mothers 6–10 weeks postnatally, which serves as the primary and key secondary outcomes for Baby Steps. As a part of the consent to BiBBS, mothers agree to the information about them and their child being used to evaluate interventions, either as intervention or control participants. A significant proportion of pregnant BiBBS women report mild to severe symptoms of depression (46%), and symptoms of anxiety (30%) [22].

### Intervention

Baby Steps is a ‘relationship-based’ antenatal parent education programme developed by the NSPCC (https://learning.nspcc.org.uk/services-children-families/baby-steps).

Baby Steps delivery begins around the 26th to the 30th week of pregnancy. The programme under evaluation differs to the original programme in that it is delivered to groups remotely but retains some face-to-face contact. To adapt to remote delivery, the service delivery team have condensed the intended nine individual sessions into six group sessions. There are two one-to-one initial sessions (one of which is in the participant's home, one of which is virtual) prior to the course commencing to help build relationships between families and practitioners. Then there are four online, remote, group sessions before the baby is born. After the baby is born there is another in person home visit, followed by two online group sessions. See Table 1 for an overview of the sessions and timings.

**Table 1 Tab1:** Overview of programme content and timings

Content	Time of delivery
**Antenatal course components**	
Initial assessment and consent	Antenatal week 1; one-to-one home visit
Evaluation questionnaires	Antenatal week 2; one-to-one virtual visit
Relationships, respect and support	Antenatal weeks 3–6; 2 group sessions
Parent-infant interactions	Antenatal weeks 6–8; 2 group sessions
**Postnatal course components**	
Re-engage families and complete evaluation questionnaires	Postnatal week 1; one-to-one home visit
Healthy bodies, healthy minds (group sessions)	Postnatal week 2; 1 group session
Understanding babies’ development and practicalities of parenthood	Postnatal week 2; 1 group session

Baby Steps sessions are facilitated by an Early Years Practitioner and a health practitioner (midwife or health visitor). The curriculum and activities for each group follow a set pattern at specific stages of pregnancy and following each baby’s birth. As the programme is now being delivered universally, any pregnant person (< 28 weeks gestation) who is living in one of the three Better Start Bradford areas is eligible to be referred to Baby Steps.

### Participants

#### Recruitment

Pregnant women are invited to join BiBBS by trained researchers who are not involved in the woman’s clinical care. This recruit takes place predominantly at Bradford Royal Infirmary’s Glucose Tolerance Test (GTT) clinic at 24–28 weeks gestation, and secondary recruitment sources in the community. If they consent, they complete a baseline questionnaire and consent for linkage of routine health and education data.

Recruitment to Baby Steps occurs through midwives asking eligible mothers to provide consent for their contact details to be shared with the Baby Steps delivery team, who then make contact to arrange a home visit.

#### Eligibility

Study participants will be pregnant women who are also participating in BiBBS and enrolled on or after the 1^ s^ May 2022. Data will be collected at the level of the mother.

Eligibility for the intervention group are:Currently pregnant and have not exceeded 24 weeks gestationLives in the Better Start Bradford areaHave consented to a referral to Baby Steps

Eligibility for the propensity score matched comparison group are:Have a child aged between 0- and 3-months during service delivery of Baby StepsNot currently receiving, and have not already received, Baby Steps in the Better Start programme at any timeProvided data in the BiBBS additional sweep at any time in the duration of service delivery

See statistical methods section for more information on how the matched control group will be created.

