**Fig. 1 Fig1:**
[figure not shown]
Directed Acyclic Graph of associations between confounders, treatment exposure, and primary outcome

Table 2 describes the covariates that we will use for propensity score matching obtained from the BiBBS baseline questionnaire completed before the child is born. All matching variables are at the level of the mother, not the child. Variables were selected to be matched upon if they were thought to have an association with both uptake of treatment, and with the outcomes (maternal sensitivity, maternal mental health), and there was empirical evidence to suggest this was the case (see references in Table 2).

**Table 2 Tab2:** Covariates for matching obtained from BiBBS baseline questionnaire

Covariates (measurement tool if relevant)	Measurement	Justification
Prenatal attachment (Prenatal Attachment Inventory)	Continuous	[13]
Prenatal Depression (PHQ-8)	Continuous	[13]
Prenatal Anxiety (GAD-7)	Continuous	[13]
Ethnicity	Categorical	[13, 41, 51]
Socioeconomic position (financial security)	Continuous	[28, 48, 51]
Mother age	Continuous	[13, 28]
Parity (first child or not)	Continuous	[48]
Speaks English	Binary	[11, 51]

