### Linear regression analyses 

After matched groups have been created, linear regression analyses will be run using group assignment as the independent variable, and the primary (maternal sensitivity) and secondary outcomes (maternal mental health) as the dependent variables. In addition to group assignment, two covariates will be included in the model: child age in days will be included as a continuous covariate, and Better Start Bradford area will be included as a categorical covariate with 3 levels. Models will be run for each outcome: maternal child sensitivity (MORS-SF), maternal depression (PHQ-8), and maternal anxiety (GAD-7).

We will conduct both Intention to Treat (ITT) analyses to ascertain the effects of enrolling in the intervention [23, 27], and per protocol analyses to ascertain the effects of receiving the treatment [50]. The ITT analyses will therefore include all mothers who enrolled in the intervention after an initial home visit, and the per protocol analyses will only include ‘completers’, defined as those who take part in at least 6 sessions (including at least one postnatal session).

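### Earlier Baby Steps attendance bars a woman from the control group but not from the intervention group, so repeat attenders have no comparable controls

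*Protocol article*

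**What the plan says.** The protocol article (Eligibility) gives a separate list for each group.

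- **Intervention:** pregnant and not beyond 24 weeks, living in the Better Start Bradford area, and consenting to referral. There is no rule on earlier attendance.
- **Control:** a child aged 0 to 3 months during service delivery, data in the additional BiBBS sweep, and no current or past programme exposure. These women must "have not already received, Baby Steps in the Better Start programme at any" time.

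On the history of the service, the section on the Baby Steps programme says that delivery became remote and condensed in March 2020, and that "Baby Steps also moved from a targeted to a universal offer in February 2022". That change removed all eligibility criteria.

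On residence, the control list is silent. The section on linear regression analyses states that "Better Start Bradford area will be included as a categorical covariate with 3 levels", and Study setting says that "the initiative is delivered in three areas: Bowling and Barkerend, Bradford Moor and Little Horton".

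**The concern.** Barring treated women from a control group is ordinary practice. The difficulty is that the intervention list has no mirror rule. A woman with an earlier course can be counted only on one side, so there is no overlap on exposure history, and this is set by rule rather than by chance. Matching cannot restore it, because no eligible control has that history.

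Aims 1 and 2 concern the universal, remotely delivered model. A repeat attender may still carry some effect of an earlier course that was targeted and may have been delivered in another form. Her outcome would then mix two exposures. In addition, the control rule takes previously targeted mothers out of the pool while such mothers stay eligible for the intervention group. In a non-randomised study that claims causal effectiveness, like-for-like eligibility is one of the main protections.

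**Working it through.** **1. The two lists side by side**

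| Criterion | Intervention | Control |
|---|---|---|
| Earlier Baby Steps | no rule | excluded |
| Lives in the Better Start area | required | not listed |

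**2. Can repeat attenders occur?** The service ran before the study window opened on 1 May 2022: the programme section describes earlier targeted delivery, and the sample size section draws on historical attendance data. Access is now open: any pregnant person under 28 weeks "who is living in one of the three Better Start Bradford areas is eligible to be referred to Baby Steps". Parity is a matching variable, so mothers with earlier children are expected. Nothing stated prevents a second enrolment. No count of such women is given.

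**3. Would matching identify them?** The Table 2 covariates are prenatal attachment, PHQ-8, GAD-7, ethnicity, financial security, age, parity and speaking English. Parity separates first-time mothers from others and does not record earlier attendance. Attachment, PHQ-8, GAD-7 and financial security would take up part of any difference in need or carry-over, so the gap is partial.

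**4. The plan's own figure.** For d = 2.35 / 4.7 = 0.50, two-sided 5% and 80% power, the two-sample t-test needs 63.8, so 64 per group (128 in total). The plan states 130 (65:65), at which power is 80.8%. The figure reproduces, and it does not depend on the eligibility rules.

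**5. Illustrative size, on assumed inputs only.** Shift = share of repeat attenders in the intervention group × carry-over in SD × 4.7.

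- Low: 0.05 × 0.25 × 4.7 = 0.06 points; 0.06 / 2.35 = 2.5% of the target difference.
- High: 0.20 × 0.50 × 4.7 = 0.47 points; 0.47 / 2.35 = 20% of the target difference.

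Neither the share nor the carry-over has a source in the documents. The formula also counts carry-over already visible in the baseline scores, which matching would partly remove, so for given inputs it overstates the shift.

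**6. Direction.** A lasting benefit from the earlier course would favour the programme. Taking previously targeted mothers out of the control pool only could leave lower-need controls, which would count against it. The documents do not give the old targeting criteria, so the net sign is unknown.

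**7. What exclusion would cost in power** (t-test, two-sided 5%, same assumed shares)

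| Share excluded | From 45, with 135 controls, d = 0.50 | From 62, with 187 controls, d = 0.50 | From 62, with 187 controls, d = 0.42 |
|---|---|---|---|
| 0% | 45: 82.4% | 62: 92.5% | 62: 81.5% |
| 5% | 43: 81.1% | 59: 91.5% | 59: 80.0% |
| 10% | 40: 78.9% | 56: 90.5% | 56: 78.4% |
| 20% | 36: 75.5% | 50: 87.9% | 50: 74.8% |

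The last two columns use the intervention group of 62 on which the recommended enrolment target is based.

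**8. Residence.** The area covariate has three levels and exactly three areas are named. A control living elsewhere would have no level in the outcome model, so the model presupposes controls from within the areas. The Abstract adds that "All participants are drawn from Born in Bradford’s Better Start (BiBBS) interventional family cohort study", and that cohort runs in parallel with Better Start Bradford, though the article does not say that its members must live in the areas. The control list therefore leaves out a condition that the model relies on.

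**The case against.** The strongest reply is that keeping repeat attenders is a choice of estimand. The offer is universal, the setting is real-world, and the ITT analysis estimates the effect of enrolling. A woman who enrols again is part of that population. This stands, and it is why a sensitivity analysis is an acceptable alternative to exclusion. It does not remove the problem that these women have no counterpart among the controls.

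A second reply is that matching on attachment, depression, anxiety and financial security removes much of any difference, that only women with an earlier pregnancy and earlier attendance are affected, and that no prevalence is given. This also stands, and it limits the point to a probably small bias of unknown sign.

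A third is that sensitivity analyses commonly belong in the SAP, which is not shown. That is fair for the sensitivity analysis. The two eligibility lists, however, are stated in the article, and they differ.

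A reader might infer three stronger points, which the documents do not support:

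- **That the groups differ by rule on access to the programme.** The three-level area covariate points to controls from within the areas, and nothing shows that women from outside are in the pool.
- **That Table 2 captures none of the risk difference.** It captures part, and no uncaptured targeting criterion can be named.
- **That power suffers because controls without an area value drop out of the model.** This would need an assumed share of such controls, for which there is no basis.

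**Conclusion.** The point holds on exposure history. As written, a woman with earlier Baby Steps can appear only in the intervention group, has no comparable control, and is not identified by any matching covariate. This follows from the text and needs no assumption beyond the existence of some repeat attenders, which the service history makes possible but does not show.

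The consequence is probably small. The illustrated 0.06 to 0.47 MORS-SF points rests wholly on assumed shares and carry-over, takes no credit for matching, and covers only one of two opposing mechanisms. No stated sample size is wrong on this account.

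On residence, only an alignment of wording between the Eligibility section and the outcome model is needed.

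**What to change.** 1. For the evaluation sample only, with access to the service unchanged, choose one of two options and state it in Eligibility:
   - require no Baby Steps in an earlier pregnancy in both groups, applied before the propensity score is estimated; or
   - keep repeat attenders in the ITT analysis and prespecify a sensitivity analysis that leaves them out and repeats the matching.
2. In the control list, state residence in one of the three Better Start Bradford areas, so that it agrees with the three-level covariate.

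**Cost.** This is a few lines of wording. BiBBS consent already covers information about intervention participation, and area is already needed for the model. Exclusion may lose a few intervention mothers and narrows the question to women new to the programme. If the share proves near 10% or more, power would fall below 80% at the 45:135 minimum and for the mental health outcomes at 62:187, and the sensitivity analysis is then the cheaper option.
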